## Data Analysis

### Sample Size

The sample size has been determined based on the primary outcome: changes in the intake of fresh fruits and fresh vegetables. Based on the relevant studies where the average fruit and vegetable intake was about 255 ± 200 g per day in edentulous elderly (17), we assume that the average fruit and vegetable intake will increase 50 g, 70 g and 245 g in patients receiving dental prostheses alone, brief dietary advice alone, or the combination dental treatment with brief dietary advice, respectively. With an anticipated 20% loss to follow-up, 30 patients are needed in each group to test the significance of dental treatment, brief dietary advice, alone or in combination with alpha set at 0.05 and with 80% power. Due to limitations in the baseline knowledge for precise sample size calculations and the efforts required for an adequate pilot study, adaptive adjustment of sample size will be performed. Sample size calculation will be re-estimated after obtaining the primary outcome of 10 patients in each group. Based on the interim analysis for adaptive design, several scenarios have been identified: (i) the original sample size estimation is appropriate and the study will be completed accordingly; (ii) the original sample size will be insufficient but will still be within the capability of recruitment of the study center, in such case the sample size will be expanded according to the adaptive design principles; (iii) the original sample size will be insufficient but too large for successful completion of the study at the study center alone, in such scenario the study will be completed as a pilot study with the original sample size and a multicenter trial will be designed and implemented based on the results.

### Statistical Software and General Requirements

Data analysis will be performed in SPSS software, version 26.0 (IBM Corp., Armonk, NY, USA). The level of statistical significance will be set at 0.05 for all tests.

### Statistical Analysis Plan

(1) Descriptive statistics will report the demographic, clinical and biological characteristics of the study population. Means with standard deviations (SD) or medians with interquartile range (IQR) will be used to describe continuous variables. Frequencies will be used to describe categorical variables.(2) The normality of clinical and biological parameters at baseline and each re-evaluation visit will be tested for normality using the Kolmogorov-Smirnov test. The homogeneity of the clinical and biological parameters at baseline and each re-evaluation visit will be tested using Levene's test.(3) ANOVA analysis will be used to test the effect of dental treatment, brief dietary advice, both dental treatment and brief dietary advice, sequence of two interventions for continuous variables with a normal distribution. The Kruskal–Wallis test will be used for non-continuous variables or continuous variables not normally distributed.

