#### Randomization

Subjects will be randomly assigned to one of four groups with a 1:1:1:1 ratio by stratified block randomization. The block size will be 8 and stratifying factors will be diabetes status and smoking. Subjects will be registered into the study by a study registrar who will assign the treatment number and organize the sequence of the bookings of the patient according to the random allocation. The registrar will not be involved in any other study procedures.

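### A normality pre-test decides whether the primary outcome gets ANOVA or Kruskal–Wallis, and the fallback yields neither the interaction nor an effect in g/day

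*Protocol article*

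**What the plan says.** Under Statistical Analysis Plan, the article says that clinical and biological parameters at baseline and each later visit "will be tested for normality using the Kolmogorov-Smirnov test", with Levene's test for homogeneity. For continuous variables with a normal distribution, ANOVA is then used "to test the effect of dental treatment, brief dietary advice, both dental treatment and brief dietary advice, sequence of two interventions". The Kruskal–Wallis "test will be used for non-continuous variables or continuous variables not normally distributed".

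The factorial effects are listed only in the ANOVA sentence. No contrast is named for Kruskal–Wallis. No other section fixes a model for the primary outcome, so this rule governs it.

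The primary outcome is the change in intake at 4 months (Food and Nutrient Intake; Sample Size). The planning figure is that intake "was about 255 ± 200 g per day in edentulous elderly". Randomization adds that the "stratifying factors will be diabetes status and smoking"; the analysis text names no covariates.

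**The concern.** This is a rule that the article states, not a detail left to a fuller document. The data decide which hypothesis is tested. On one branch the 2 × 2 effects are examined on the g/day scale. On the other there is a rank test whose contrasts are not defined.

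The design exists to separate the contributions of the dental and dietary components, and the stated hypothesis concerns their combination. If the gate sends the primary outcome to Kruskal–Wallis, the interaction and the size of every effect in g/day drop out of the primary analysis.

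The gate is also loosely defined. The text does not say whether normality is checked on visit values, change scores or model residuals, or whether by group or pooled. These choices alter which test becomes primary.

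**Working it through.** **Inputs.** From Sample Size: SD 200 g/day, gains of 50 g (dental), 70 g (diet) and 245 g (both), 30 per group, 20% loss, alpha 0.05, 80% power. Assumed: two-sided test, control change 0, SD 200 applied to the change (equal to the intake SD only if the baseline-to-4-month correlation is 0.5).

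**1. Effects implied by the plan**
- Dental main effect: [(50 − 0) + (245 − 70)]/2 = 112.5 g
- Dietary main effect: [(70 − 0) + (245 − 50)]/2 = 132.5 g
- Interaction: 245 − 50 − 70 + 0 = 125 g

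**2. The plan's own size.** For the dental main effect, n per margin = 2 × (1.96 + 0.8416)² × 200²/112.5² = 49.6, so 50, or 25 per group. Dividing by 0.8 gives 31.25, so 32, against 30 stated. With 30 × 0.8 = 24 evaluable per group, SE = 200 × √(2/48) = 40.8 g and power is 78% for dental and 89% for diet (noncentral t). The 30 per group is thus consistent, within two patients, with factorial main effects in g/day. A four-group Kruskal–Wallis does not test these contrasts.

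**3. What Kruskal–Wallis delivers** (simulation, 24 per group)
- Four groups, planned effects, normal errors: rejects in 97%.
- Four groups, only diet works (132.5 g; dental effect and interaction zero), normal errors: still rejects in 74%. A significant result does not say which component worked.
- Two-level margins: rank tests of dental and of diet are possible. The interaction and a g/day estimate are not.

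**4. How likely the switch is.** A normal curve with mean 255 and SD 200 puts Φ(−255/200) = Φ(−1.275) = 10% below zero, which is impossible for intake. Rejection rates of the Kolmogorov–Smirnov test (Lilliefors form, alpha 0.05, 96 patients pooled, gamma or lognormal intake with that mean and SD, correlation 0.3–0.7):
- Raw baseline intake: about 97% to nearly 100%
- 4-month intake with the planned shifts: about 75–93%
- Change scores with the planned shifts: about 24–60%
- Change scores without shifts: about 46–90%

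With a gamma (shape 2) error placed directly on the change, plus the planned shifts, the pooled rate is 68%; hence the rough range of 25–70% for change scores. Even with exactly normal data, testing each of four groups triggers a rejection with probability 1 − 0.95⁴ = 18.5% (18% simulated).

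**5. Value of baseline adjustment.** With SD 200 at both visits and correlation r, the change-score SD is 200√(2(1 − r)) and the baseline-adjusted SD is 200√(1 − r²). The variance ratio is (1 + r)/2. The article gives no r, so a range is shown.

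| r | SD change | SD adjusted | Dental power, change | Dental power, adjusted |
|---|---|---|---|---|
| 0.3 | 236.6 | 190.8 | 63% | 82% |
| 0.5 | 200.0 | 173.2 | 78% | 88% |
| 0.7 | 154.9 | 142.8 | 94% | 97% |

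**The case against.** The case against has several parts, and much of it stands.

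- A reader might infer that Kruskal–Wallis cannot test the dental or dietary effect at all. The article does not say that the test is run across four groups, and on two-level margins it would test both. What is lost in every form is the interaction and the g/day estimate.
- A reader might expect the switch to cost power, since with normal errors and a diet-only effect Kruskal–Wallis reaches 74% against 89% for the factorial contrast. That is mostly the wrong case, because the rule invokes Kruskal–Wallis when normality is rejected. With gamma errors the figures are 92% against 89–90%, and with lognormal errors 97% against 88–89%. For heavy-tailed change scores they are 84–91% against 88–89%, depending on how the correlated visits are simulated. The comparison also sets a 3-df test against a 1-df one. No power loss should be claimed.
- A reader might say that the ANOVA ignores baseline. It does not: the outcome is a change, and an unadjusted change-score ANOVA in a randomised trial is valid.
- On diabetes and smoking the article is silent, and covariates are commonly left to a fuller plan. That is no error.
- The rate of 97% or more concerns raw intake. For the change itself the risk is much less certain. It rests on assumed shapes and on an SD from another study, whereas this trial selects on inadequate intake and uses three recalls.

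None of this removes the gate, which is stated and covers the primary outcome.

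**Conclusion.** The point holds in this form: as written, a distributional pre-test can move the primary analysis of a 2 × 2 trial to a method with no named contrast, no interaction and no effect in g/day. The plan's own assumptions imply a 125 g interaction if the control change is zero.

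The probability of the switch cannot be fixed from the article. It is near certain if raw visit values are tested and intake is skewed, and very roughly 25–70% if change scores are tested. Both figures depend on assumed gamma or lognormal shapes.

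The documents do not support saying that the factorial question is bound to go unanswered, that Kruskal–Wallis is less powerful here, or that baseline is ignored.

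The linear model does not make the interaction well powered. At 24 per group, SE = 200 × √(4/24) = 81.7 g and power for 125 g is about 33%. It does provide an estimate with a confidence interval.

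**What to change.** State one primary model that applies whatever any pre-test shows: a linear model of 4-month fruit and vegetable intake on DE, DI and DE × DI, with baseline intake as covariate. Report effects in g/day with 95% CIs from heteroscedasticity-robust or bootstrap standard errors. With baseline in the model, the DE, DI and interaction coefficients are the same whether the response is 4-month intake or the change, so the primary outcome is preserved.

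Drop the Kolmogorov–Smirnov and Levene gate for the primary outcome. Keep rank-based or transformed analyses as sensitivity analyses only. Adding diabetes status and smoking is an optional improvement that needs no new data.

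The cost is wording, plus one degree of freedom for baseline and about two more for the strata. All variables are already collected and the named software can fit the model. The change should be made before any unblinded outcome data are seen, including the sample-size re-estimation at 10 patients per group.

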### Data Quality and Assurance

All investigators involved in this study will be trained appropriately for the standard operating procedures including the questionnaire conduction, blood sampling and preservation, presurgical examinations and treatment (regarding periodontal diseases, caries, missing teeth and soft tissue disorders) and delivery of interventions.

(1) The 24-h dietary recall will be conducted by clinical nutrition specialists trained appropriately for the standardized interviewing procedures and assessment of dietary intake. The inter- and intra-examiner reliability with respect to the measurement of fresh foods and fresh vegetables intake will be assessed by the intraclass correlation coefficient (ICC). In order to ensure optimal inter- and intra-examiner reliability, ICCs needs to be more than 0.75.(2) The therapists, who will deliver the dental intervention, will be experienced specialists in implant dentistry fulfilling the Shanghai requirements. Treatment will be provided to the satisfaction of the clinician and patient. For logistic reasons, five therapists will be included in this study.(3) The investigator who performs dietary interventions will be trained in delivering a standardized dietary instruction session including the verbal instruction and demonstration of the pamphlet. In addition, the investigator will be trained in the use of questionnaires.

Regular monitoring for assuring protocol compliance, and data quality at the clinical site, including review of source documents and records, consent forms, etc will be performed by an investigator trained in both GCP and the specific procedures. Furthermore, the clinical research coordinator will audit the case report forms for the first few patients to ensure correct filling of forms. The study will also be monitored by the compliance office of the National Clinical Research Center of Oral Diseases and Clinical Research Center of the 9th People's Hospital.

### Confidentiality

All trial-related data will be stored securely at Shanghai PerioImplant Innovation Center. The participant information will be stored in locked cabinets with limited access. All data will be anonymized by assigning a Research ID used for data collection and processing to maintain participant confidentiality. All records containing personal identifiers will be stored separately from study records identified by the research ID number.

Tooth loss is frequently incremental over the course of life and subjects in the population present with a spectrum of severity of loss of masticatory function. This study will focus on the more severe end of the spectrum as these subjects are both likely to suffer from greater changes in diet and more likely to show improvements in masticatory function because of tooth replacement. It will also recruit aging subjects who represent most edentulous subjects. Additional studies expanding the observations to milder forms of edentulism will be needed. To ensure that subjects will suffer from both masticatory dysfunction and a degree of malnutrition, an inclusion criterion has been added in terms of verification of poor fruit, vegetable, or protein intake. Pilot nutritional analysis of edentulous subjects reporting for treatment in the specific setting has verified that most of them reported at least one aspect of impairment and fit the inclusion criteria. These aspects are important for the external applicability of the results of the trial and ongoing epidemiologic research will provide additional information.

The definition of both the dental intervention and the nutrition education are also notable. To address masticatory dysfunction this study will employ fixed dentures supported by dental implants—a well-defined intervention routinely performed in the specific setting—as these have been shown to provide better objective and subjective chewing benefits (11). The masticatory function will be restored to provide at least 10 occluding pairs of teeth, a number generally considered compatible with adequate function (22, 46).

HBM has been used in aiding behavior change intervention for decades, and it has been applied to Asian populations. With the HBM-based nutrition education, the objective is to motivate participants from the pre-contemplative stage to the contemplate stage, and even to preparatory stage with the materials provided. Combining with the dental intervention which will solve the physical barrier, the hypothesis is that participants will progress to the executive stage at home. During the follow-up period, the importance of dietary intake will be reinforced to help them to stay in the maintenance stage. The intervention, its instruments and their delivery have been tailored to local circumstances, evaluated, and revised in our pilot study before implemented for the trial. Details are presented in the online appendices as a potential resource for additional trials.

While the equipoise to justify randomization is strong, recruiting patients with edentulism/terminal dentition for a trial is challenging due to the severity of the condition and the impact on quality of life. The opportunity arises in the specific setting due to the waiting list for treatment that justifies the delay in the delivery of the care initially sought by the patient.

Lastly the choice of the primary outcome has been complex due to the limited previous information on clinically relevant outcomes and the need to maintain the size of this trial within the recruitment possibilities of the single center. The choice to focus on a proxy outcome—changes in fresh fruits and fresh vegetables consumption—as the primary outcome, rather than a health gain measure, is based on the need to establish the effectiveness of the treatment regimen and logistic considerations. The limitation of 24-h recall method in providing an accurate estimate of long-term energy intake has been realized. Thus, the study plans to combine food frequency questionnaires which replied on generic rather than specific memory to offer detailed assessment of the study period. Furthermore, the study plans to assess a wide palette of secondary outcome that will provide insight into mechanisms of a potential benefit by exploring both biochemical markers, metabolomics and changes in the oral-gut microbiome axis and functional quality of life instruments.

The relatively short follow-up time for the factorial design component of the study is adequate to assess the efficacy of the interventions. The 12-month extension is relevant as it will supply critical information about retention of subjects in the trial and medium-term compliance with the dietary intervention and effectiveness of the dental intervention. It will also provide the basis for future longer-term trials focusing on health outcomes.

## Ethics Statement

The studies involving human participants were reviewed and approved by the Institutional Review Board of the Shanghai Ninth People's Hospital, Shanghai Jiao Tong University School of Medicine (Approval No. SH9H-2021-T321-3). The patients/participants provided their written informed consent to participate in this study.

## Abbreviations

DE: dental intervention
DI: dietary intervention
HbA1c: glycated hemoglobin
CRF: case report form
CBCT: Cone beam computed tomography
hs-CRP: high-sensitivity-C-reactive protein
TNF-α: tumor necrosis factor-α
IL-1β: Interleukin-1β
IL-6: Interleukin-6
Co Q10: coenzyme Q10
LS-MS: liquid chromatography-mass spectrometry
HDL: high density lipoprotein
LDL: low density lipoprotein
HBM: health belief model.
